### Safety evaluation

Monitoring and Recording of Adverse Events: Investigators will continuously monitor patient safety using specific questionnaires and record all adverse events (AEs) throughout the study process. Records will detail the relationship between the adverse events and the study treatment, onset and resolution dates, severity, actions taken, and whether the adverse event resulted in withdrawal from the trial. These findings will be summarized at the conclusion of the study.

Laboratory and Physical Examinations: Routine blood tests, liver function, renal function, and electrocardiography (ECG) will be performed at baseline and after 12 weeks of treatment.

### Data analysis

Software and Data Handling: All statistical analyses will be performed by an independent statistician using SPSS 25.0 software (IBM, Armonk, NY). Missing data will be imputed using the Last Observation Carried Forward (LOCF) method.

Normality and Continuous Variables: Measurement data will be assessed for normality using the Shapiro-Wilk (S-K) test. Data conforming to a normal distribution will be expressed as mean ± standard deviation (SD). Intra-group comparisons (pre- and post-treatment) will be analyzed using the paired samples t-test, while inter-group comparisons will be performed using the independent samples t-test. Measurement data that does not follow a normal distribution will be analyzed using non-parametric rank-sum tests.

Categorical Variables and Significance: Enumeration data (categorical data) will be presented as percentages or constituent ratios, and differences between groups will be analyzed using the Chi-square (χ²) test. All statistical tests will be two-sided, with the significance level set at αt 0.05. A P-value < 0.05 will be considered statistically significant.

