### Removal criteria

Cases that were mistakenly included and do not meet the inclusion criteria.

Patients who receive other treatments during the study period (e.g., surgical treatments for breast cancer-related lymphedema, including lymphaticovenular anastomosis [LVA], debulking surgery, vascularized lymph node transfer [VLNT], or liposuction).Patients with poor compliance or an insufficient observation period.Patients with incomplete study data.Patients who are lost to follow-up.Patients who experience severe adverse events during the study period, or are diagnosed with other major diseases, tumor recurrence, or metastasis, rendering the study protocol no longer applicable.

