### Sample size calculation

Given the novel and exploratory nature of the intervention for BCRL in this study, a minimum clinical sample size of 30 participants per group was selected (18),Assuming equal sample sizes for both groups and anticipating a 20% dropout rate, the total sample size was calculated as follows: N = 30o2×(1 + 20%)=72. Therefore, a total of 72 participants will be enrolled, with 36 participants in each group.(Reference: Whitehead AL, Julious SA, Cooper CL, Campbell MJ. Estimating the sample size for a pilot randomized trial to minimize the overall trial sample size for the external pilot and main trial for a continuous outcome variable. Statistical Methods in Medical Research. 2016;25 (3):1057-73).

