Treatment Course: Preventive intervention begins on the first day before surgery and continues daily until the third day after surgery. Subsequently, all patients will receive scheduled treatments twice a week (every Monday and Thursday at 10:00 AM) for 30 minutes per session. This phase consists of 8 consecutive scheduled sessions, extending to one month post-operation, for a total of 12 interventions.

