### Follow-up

Since the onset of lymphedema typically occurs between 3 months and 3 years postoperatively, peaking at 18 months (5), the follow-up period is established as 1.5 years postoperatively. From the completion of the intervention until 1.5 years postoperatively, follow-up will be conducted once a month via telephone or WeChat. The content of these follow-ups includes the visual analogue scale (VAS) for perceived swelling and lymphedema-related symptoms. Additionally, an in-person appointment will be scheduled at 1.5 years postoperatively to collect data on upper limb circumference, edema stage, and severity.

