### Primary outcome

The incidence and time of onset of lymphedema from the postoperative period until the end of follow-up.

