Postoperative Day 2 (T3)											
Postoperative Day 3 (T4)											
Scheduled Treatment 1 (T5)											
Scheduled Treatment 2 (T6)											
Scheduled Treatment 3 (T7)											
Scheduled Treatment 4 (T8)											
Scheduled Treatment 5 (T9)											
Scheduled Treatment 6 (T10)											
Scheduled Treatment 7 (T11)											
Scheduled Treatment 8 (T12)											
Follow-up 1 (T13)											
Follow-up 2 (T14)											
Follow-up 3 (T15)											
Follow-up 4 (T16)											
Follow-up 5 (T17)											
Follow-up 6 (T18)											
Follow-up 7 (T19)											
Follow-up 8 (T20)											
Follow-up 9 (T21)											
Follow-up 10 (T22)											
Follow-up 11 (T23)											
Follow-up 12 (T24)											
Follow-up 13 (T25)											
Follow-up 14 (T26)											
Follow-up 15 (T27)											
Follow-up 16 (T28)											
Follow-up 17 (T29)											

Comparison of Limb Circumference Changes, Edema Staging, and Severity: Changes in the circumference, edema stage, and severity of the affected limb will be observed at baseline (T0), before and after treatments from preoperative to postoperative day 3 (T1a/b-T4a/b), before and after twice-weekly post-discharge treatments (T5a/b-T12a/b), and at 18 months postoperatively (T29). The mean values and differences in circumference before and after treatment will be compared between the two groups to evaluate the effect of treatment on limb edema. Staging and measurement standards are detailed in **Table 4**.

**Table 4 T4:** Data collection form for upper limb circumference, edema staging, and severity.

Name: Age: Operated limb: Date of surgery:													
Upper limb circumference measurement							Edema stage				Edema severity		
Measurement timepoint	Measured limb	Palmar crease	Wrist crease	10 cm above wrist crease	Elbow crease	5 cm above elbow crease	Stage 0	Stage I	Stage II	Stage III	Mild	Moderate	Severe
Preoperative (T1)	L												
	R												
Postoperative Day 1 Pre-treatment T2a	L												
	R												
Postoperative Day 1 Post-treatment T2b	L												
	R												
Postoperative Day 2 Pre-treatment T3a	L												
	R												
Postoperative Day 2 Post-treatment T3b	L												
	R												
Postoperative Day 3 Pre-treatment T4a	L												
	R												
Postoperative Day 3 Post-treatment T4b	L												
	R												
Scheduled Treatment 1 Pre-treatment T5a	L												
	R												
Scheduled Treatment 1 Post-treatment T5b	L												
	R												

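### LOCF is set for all missing data, so a missing 18-month limb status would be filled from about month 1, and the removal criteria contradict the rule

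*Protocol article*

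**What the plan says.** Data analysis gives one rule for every outcome: "Missing data will be imputed using the Last Observation Carried Forward (LOCF) method". The primary outcome is "The incidence and time of onset of lymphedema from the postoperative period until the end of follow-up". It comes with no diagnostic threshold and no statement of which assessment establishes onset.

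Under Secondary outcomes and in Table 4, limb circumference, edema stage and severity are recorded at baseline, around the inpatient and outpatient sessions up to T12, and then at T29. The treatment course places the last outpatient session at about month 1: "extending to one month post-operation, for a total of 12 interventions". Between T12 and T29, "follow-up will be conducted once a month via telephone or WeChat", covering the swelling VAS and the symptom scores. The only late in-person visit is at 18 months.

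The length of follow-up is justified with "Since the onset of lymphedema typically occurs between 3 months and 3 years postoperatively, peaking at 18 months". The sample size is set "anticipating a 20% dropout rate". The Removal criteria list "Patients who are lost to follow-up", and also those with incomplete data or too short an observation period.

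**The concern.** LOCF stands in for a missing value only if the status is unlikely to change after the last observation. Here the protocol says the opposite: on its own account, most onsets fall after T12. Someone measured at month 1 and absent at month 18 would be given a limb status taken before the disease typically starts. The same rule also fails for time of onset, because a lost participant is known to be event-free only up to the last negative assessment and not up to month 18.

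The Removal criteria add a second problem. Read in the usual way, they take the same participants out of the analysis. One section deletes them and another imputes them, mostly as event-free. With both rules in the text, the choice could be made after the data are seen, and the two rules give different primary results.

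**Working it through.** **The plan's own figure.** The only stated calculation is 30 × 2 × (1 + 0.20) = 72, or 36 per group. It reproduces. No event rate, effect size or power is given, so none can be checked.

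**Inputs from the protocol**
- Loss d = 20% (Sample size calculation).
- Incidence p: 58.3% after axillary dissection, given as an upper figure (Introduction), and about one quarter (Discussion). Both are background figures, used here as a range.
- Last limb measurement before T29: T12, about month 1.

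**Assumptions**
- Loss is unrelated to outcome.
- Monthly symptom contacts do not establish onset.
- s is the share of lost participants classed as cases at T12; the main calculation uses s = 0.
- Unequal losses of 25% v 15% and 30% v 10% are illustrations.

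**Incidence under LOCF** = (1 − d) × p + d × s. With s = 0 this is p × (1 − d):
- p = 25%: 0.25 × 0.8 = 20.0%
- p = 58.3%: 0.583 × 0.8 = 46.6%

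Per arm, 36 × 0.2 = 7.2 participants are lost. Among them, 7.2 × 0.25 = 1.8 to 7.2 × 0.583 = 4.2 eventual cases are recorded as event-free.

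**If some cases are already visible at T12.** Suppose 10% of eventual cases are, so s = 0.1 × p. The results become 0.200 + 0.2 × 0.025 = 20.5% and 0.466 + 0.2 × 0.0583 = 47.8%. Between 94% and 97.5% of lost participants are still counted as event-free.

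**Equal loss with a true effect.** Both incidences are multiplied by 0.8, so the risk difference is also multiplied by 0.8 and the risk ratio is unchanged. With an assumed halving of incidence:

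| Sham incidence | True difference | Under LOCF | Power, complete data (36 per arm) | Power, LOCF | Power, completers (about 29 per arm) |
|---|---|---|---|---|---|
| 25% | 12.5 points | 10.0 points | 27% | 22% | 23% |
| 58.3% | 29.1 points | 23.3 points | 71% | 55% | 61% |

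**Unequal loss, no true effect.** The false difference is p × (difference in loss):
- 25% v 15%: 0.25 × 0.10 = 2.5 points, to 0.583 × 0.10 = 5.8 points
- 30% v 10%: 0.25 × 0.20 = 5.0 points, to 0.583 × 0.20 = 11.7 points

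The arm with more loss looks better. At 30% loss on TEAS and 10% on sham, the apparent risk ratio is 0.70/0.90 = 0.78; with the losses reversed it is 0.90/0.70 = 1.29.

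**The case against.** The strongest objection is that the protocol does not settle that lost participants will be counted as event-free. A reader might infer that nearly all of them will be. The text supports this only conditionally, for three reasons.
- Under the Removal criteria they would leave the analysis. This stands, and it makes the defect a conflict between two rules as well as a poor imputation method.
- The primary outcome has no diagnostic definition. If monthly symptom scores can establish onset, the value carried is the last contact. The bias is then smaller but does not disappear, because the rest of the risk period is still treated as event-free.
- The direction depends on s being below p. The limitations paragraph allows onset immediately after surgery, and the mild category in Table 4 is any circumference difference under 3 cm, with no lower bound. Early swelling at T12 could be carried forward as a case. That is an error in the other direction and does not rescue LOCF.

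Three further inferences are tempting.
- That LOCF makes standard errors too small for the primary outcome. In the scenario calculated here it does not: each imputed status behaves as a binary outcome with probability p(1 − d), and the harm is attenuation and lost power.
- That LOCF freezes early postoperative VAS scores as 18-month values. VAS and symptoms are collected monthly to T29, so this applies only to participants lost very early.
- That equal loss distorts the relative effect. With no cases at T12 the risk ratio is unchanged.

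Data collection and management promises efforts to supplement missing outcome data for participants who discontinue or deviate. That may reduce the amount missing, but it does not say how the remainder is handled.

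**Conclusion.** The point holds in conditional form. If LOCF is applied to the primary outcome as written, a missing 18-month limb status is replaced by one from about month 1, before the protocol's typical onset window. The Removal criteria prescribe a different treatment of the same participants, and the text does not say which rule prevails.

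At 20% loss, incidence is understated by 5.0 points if it is 25% and by 11.7 points if it is 58.3%. Equal loss costs one fifth of the risk difference and some power. Unequal loss can create a false difference in either direction: 2.5 to 5.8 points at 25% v 15%, and 5.0 to 11.7 points at 30% v 10%. These sizes rest on loss unrelated to outcome, no cases at T12, onset not established by symptom contacts, and background event rates. The unequal-loss patterns and the halving of incidence are assumptions and do not come from the protocol.

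**What to change.** 1. Delete LOCF for the primary outcome, and reconcile Data analysis with the Removal criteria so that all randomised participants stay in the analysis. Deleting LOCF alone is not enough, since the Removal criteria would then leave a completers-only analysis.
2. Either censor lost participants at their last negative assessment, in a time-to-event analysis that allows for the gap between T12 and T29, or impute 18-month status by arm with a parsimonious multiple imputation model using the monthly scores already collected. With about 29 completers per arm (36 × 0.8 = 28.8) the model must be small, and participants lost early will contribute few predictors.
3. Add a sensitivity analysis that counts missing participants as cases in one arm and in both.
4. For repeated VAS, symptom and circumference data, use a mixed model on the observed values.

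The cost is analysis wording and some extra analysis, with no new visits. Intervals will be wider than LOCF would show. With 10 participants enrolled by July 2025 and follow-up planned to June 2027, the change can be fixed before the 18-month data exist.

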### Secondary outcomes

Visual Analogue Scale (VAS) for Perceived Swelling: Changes in the VAS score for perceived swelling will be observed at the following time points: before treatment (T0), from preoperative to postoperative day 3 (T1-T4), upon completion of twice-weekly post-discharge treatments (T5-T12), and during monthly follow-ups until 18 months postoperatively (T13-T29). Data will be recorded in the VAS data collection form (see **Figure 3** and **Table 2**).

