**Figure 3 f3:**
[figure not shown]
Visual simulation score.

**Table 2 T2:** Data collection form for visual analogue scale (VAS) of perceived swelling.

Name: Age: Operated limb: Date of surgery:					
Assessment timepoint	0 Points No swelling	1-3 Points mild swelling, tolerable	4-6 Points intermittent swelling, does not affect rest	7-9 Points marked swelling, affects rest, difficult to tolerate	10 Points severe swelling, unbearable, affects daily life (sleep, activity, diet, etc.)
Preoperative (T1)					
Postoperative Day 1 (T2)					
Postoperative Day 2 (T3)					
Postoperative Day 3 (T4)					
Scheduled Treatment 1 (T5)					
Scheduled Treatment 2 (T6)					
Scheduled Treatment 3 (T7)					
Scheduled Treatment 4 (T8)					
Scheduled Treatment 5 (T9)					
Scheduled Treatment 6 (T10)					
Scheduled Treatment 7 (T11)					
Scheduled Treatment 8 (T12)					
Follow-up 1 (T13)					
Follow-up 2 (T14)					
Follow-up 3 (T15)					
Follow-up 4 (T16)					
Follow-up 5 (T17)					
Follow-up 6 (T18)					
Follow-up 7 (T19)					
Follow-up 8 (T20)					
Follow-up 9 (T21)					
Follow-up 10 (T22)					
Follow-up 11 (T23)					
Follow-up 12 (T24)					
Follow-up 13 (T25)					
Follow-up 14 (T26)					
Follow-up 15 (T27)					
Follow-up 16 (T28)					
Follow-up 17 (T29)					

Lymphedema-related Symptoms: Lymphedema-related symptoms will be observed at baseline (T0), from preoperative to postoperative day 3 (T1-T4), upon completion of twice-weekly post-discharge treatments (T5-T12), and during monthly follow-ups until 18 months postoperatively (T13-T29). The symptom scale includes items such as swelling, tightness, heat, firmness, numbness, heaviness, tingling, pain, general discomfort, distress, and weakness. Each item is scored on a scale of 0 to 10, where 0 indicates “no sensation” and 10 indicates “intense sensation” (see **Table 3**).

**Table 3 T3:** Data collection form for lymphedema-related symptom scores.

Name: Age: Operated limb: Date of surgery:											
Items	No sensation 								Intense sensation		
	0	1	2	3	4	5	6	7	8	9	10
Swelling											
Tightness											
Heat											
Firmness											
Numbness											
Heaviness											
Tingling											
Pain											
General discomfort											
Distress											
Weakness											
Total score											
Assessment timepoint	Swelling	Tightness	Heat	Firmness	Numbness	Heaviness	Tingling	Pain	General discomfort	Distress	Weakness
Preoperative (T1)											
Postoperative Day 1 (T2)											

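### Continuous secondary outcomes get unadjusted t-tests at 0.05 with no key time point and no adjustment for baseline, and three of the data forms have no T0 row

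*Protocol article*

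**What the plan says.** The Data analysis section assigns methods by type of variable. For normally distributed measurement data: "Intra-group comparisons (pre- and post-treatment) will be analyzed using the paired samples t-test, while inter-group comparisons will be performed using the independent samples t-test". Otherwise: "Measurement data that does not follow a normal distribution will be analyzed using non-parametric rank-sum tests". The threshold is common to all tests: "A P-value < 0.05 will be considered statistically significant". The section names no covariate, no repeated-measures method and no time point at which a secondary outcome is to be judged.

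The Secondary outcomes section sets the schedule:

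- Swelling VAS: T0, then T1 to T29.
- Symptom scale, 11 items with a total score in Table 3: T0, then T1 to T29.
- Circumference at five sites: T0, before and after each of the 12 sessions (T1a/b to T12a/b), and T29. Here the text adds that "The mean values and differences in circumference before and after treatment will be compared between the two groups".
- Skin thickness at five points: T0, T2, T12 and T29.
- Three serum markers: T0, T4 and T12.

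The forms do not match this schedule. Tables 2, 3 and 4 begin at the row "Preoperative (T1") and have no T0 row. Table 4 has a single T1 row where the text requires T1a and T1b. Table 5, for skin thickness, does have a T0 row.

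**The concern.** A two-sample t-test takes one number per participant. With up to 29 post-baseline values per outcome and no rule for choosing among them, the natural use of the stated method is one test per visit, each at 0.05. An isolated significant visit is then likely even if TEAS does nothing.

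A t-test on follow-up values also ignores the T0 measurement that the schedule already collects. In a trial of 72 participants that precision matters.

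The within-arm paired test answers a different question. Both arms undergo axillary dissection and both receive compression, manual drainage and exercises under Basic treatment. A change from before to after within one arm therefore mixes any treatment effect with the course common to both arms. A result that is significant in one arm and not in the other is easily misread as efficacy.

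Finally, any use of T0 depends on its being recorded, and three forms give no place for it.

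**Working it through.** **Inputs.** From the protocol: 30 evaluable per arm (Sample size calculation), two-sided 0.05 (Data analysis), and the schedule above. The protocol's only related figure is the total, 30 × 2 × (1 + 0.20) = 72, which reproduces. It gives no effect size, SD, power or correlation for any continuous outcome, so those below are assumptions.

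**1. Number of between-group tests after T0**, with one summary per outcome and each serum marker counted separately: VAS 29, symptom total 29, circumference 23 (Table 4 rows after T1: 2 × 11 + 1), skin thickness 3, serum 3 × 2 = 6. The sum is 90. With no true effect, 90 × 0.05 = 4.5 significant results are expected if every visit is tested.

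**2. Chance of at least one false positive over 29 VAS visits.** If visits were independent: 1 − 0.95^29 = 77%. For correlated visits, from simulation (20,000 trials, 30 per arm, two-sample t-test at each visit):

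| Assumed correlation | Equal between all visits | Decaying with distance, AR(1) |
|---|---|---|
| 0.5 | 49% | 71% |
| 0.7 | 34% | 63% |
| 0.8 | 26% | 56% |
| 0.9 | 17% | 41% |

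The range is 17–77%, against 5% for one named comparison.

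**3. Precision.** Take the follow-up SD as 1, the same SD at baseline, and baseline–outcome correlation r. The SD that matters is 1 for a follow-up-value t-test, √(2(1 − r)) for a change-score t-test and √(1 − r²) for ANCOVA. Power is approximately Φ(d / (SD × √(2/30)) − 1.96). For d = 0.5, d / √(2/30) = 0.5 / 0.258 = 1.936. At r = 0.7:

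- follow-up value: 1.936 − 1.96 = −0.02, power 49%
- change: 1.936 / 0.775 − 1.96 = 0.54, power 71%
- ANCOVA: 1.936 / 0.714 − 1.96 = 0.75, power 77%

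| r | Follow-up value | Change | ANCOVA |
|---|---|---|---|
| 0.3 | 49% | 37% | 53% |
| 0.5 | 49% | 49% | 61% |
| 0.7 | 49% | 71% | 77% |
| 0.9 | 49% | 99% | 99% |

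ANCOVA is never behind in this table. Change scores lose to follow-up values at low r.

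**4. Paired tests with no treatment effect.** Let both arms shift by the same amount, in SDs of the change, with 30 per arm (noncentral t). At a shift of 0.5 SD, the TEAS arm's paired test is significant in 75% of trials; at 0.8 SD, in 99%. At 0.36 SD, each arm is significant with probability 0.479, so exactly one arm is significant in 2 × 0.479 × 0.521 = 50% of trials.

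**5. Forms against text.** Measurement timepoint defines T0 as before treatment and places T1 in the inpatient treatment phase, so they are distinct. The text puts T0 in the schedule for VAS, symptoms and circumference; Tables 2, 3 and 4 have no row for it. For circumference the text lists 24 + 1 = 25 post-T0 measurements, and Table 4 has 1 + 22 + 1 = 24 rows.

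**The case against.** Several stronger readings are tempting, and the protocol does not support them.

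- **Every item will be tested at every visit.** One could count 12 symptom scores × 29 visits = 348 tests. The protocol names types of test and does not say this. Table 3 has a total score, and 348 counts that total alongside its own 11 components. Per-visit testing is itself an inference, though a close one, since no summary measure or key visit is named.
- **Baseline is wasted throughout.** For circumference, before/after differences are to be compared between groups. If these are changes from T0, the remaining variance gain from ANCOVA at r = 0.7 is only 15%, since (1 − r²) / (2(1 − r)) = 0.85. They may instead be differences within a session; the text does not settle it. For VAS and symptoms, entry requires no preoperative upper limb lymphedema, so T0 is probably near zero and adjustment gains little.
- **The plan credits natural recovery to TEAS.** Nothing says that the paired tests decide efficacy, and the Discussion plans to evaluate differences between TEAS and sham. After surgery the common course may also be worsening rather than recovery. What stands is the risk of misreading.
- **The untreated baseline will be lost.** The text requires T0, the case report forms are not shown, and a preoperative row exists. What stands is that the printed forms and the text disagree.

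It may also be said that time points and multiplicity for secondary outcomes can be left to an analysis plan. That would answer silence. Here a method is stated, and a later plan would have to replace it.

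A mixed model over all visits is not a free remedy. An unstructured covariance over 29 visits has 29 × 30 / 2 = 435 parameters for at most 72 participants, and the scores may be skewed.

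**Conclusion.** The point holds for the continuous secondary outcomes only. The stated tests are unadjusted, use 0.05 throughout and name no key time point. If they are applied at each visit, the false-positive chance for VAS alone is about 17–77%, and where in that range depends on an assumed correlation. The precision loss is material where baseline correlation is high: 49% power against 77% at an assumed r of 0.7 and 0.5 SD effect. Most of that gap closes (71%) if changes from T0 are what is compared. The gain is small for outcomes that start near zero. Within-arm paired tests give no evidence on the effect of TEAS over sham. The mismatch between forms and text rests on no statistical assumption. The primary outcome, incidence and time of onset of lymphedema, does not depend on any of this, so the change is worth making but does not decide the trial's main conclusion.

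**What to change.** - For each continuous secondary outcome, name one key time point, for example T12, or T29 where it is measured. Serum markers end at T12.
- Compare the arms there by ANCOVA with the T0 value and centre as covariates. Add a rank-based or bootstrap sensitivity analysis for skewed scores.
- Analyse the symptom total rather than each item.
- Report other visits and all within-group tests as descriptive, without claims of significance.
- If a mixed model is preferred, restrict it to a few key visits or state a parsimonious covariance structure.
- Reconcile the forms with the text: add a T0 row to Tables 2, 3 and 4, and T1a and T1b rows to Table 4. Only 10 participants had been enrolled by July 2025 (Trial status), so at that date most baselines were still to be taken.

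The cost is slightly more analysis work, fewer formally tested visits and a form revision. The measurement schedule in the text does not change.

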Scheduled Treatment 2 Pre-treatment T6a	L												
	R												
Scheduled Treatment 2 Post-treatment T6b	L												
	R												
Scheduled Treatment 3 Pre-treatment T7a	L												
	R												
Scheduled Treatment 3 Post-treatment T7b	L												
	R												
Scheduled Treatment 4 Pre-treatment T8a	L												
	R												
Scheduled Treatment 4 Post-treatment T8b	L												
	R												
Scheduled Treatment 5 Pre-treatment T9a	L												
	R												
Scheduled Treatment 5 Post-treatment T9b	L												
	R												
Scheduled Treatment 6 Pre-treatment T10a	L												
	R												
Scheduled Treatment 6 Post-treatment T10b	L												
	R												
Scheduled Treatment 7 Pre-treatment T11a	L												
	R												
Scheduled Treatment 7 Post-treatment T11b	L												
	R												
Scheduled Treatment 8 Pre-treatment T12a	L												
	R												
Scheduled Treatment 8 Post-treatment T12b	L												
	R												
18 Months Postoperative (T29)	L												
	R												

Edema Staging:.

ISL Staging classifies lymphedema into 4 stages based on severity:

Stage 0: Latent or subclinical stage; no obvious limb swelling, no visible clinical symptoms.

Stage I: Obvious swelling with pitting edema; swelling subsides upon limb elevation.

Stage II: Swelling does not subside with elevation; early stage presents as pitting edema, while late stage becomes non-pitting due to subcutaneous fat deposition and fibrosis.

Stage III: Non-pitting edema with elephantiasis; skin thickening, roughness, folds, hyperpigmentation, loss of elasticity, and severe fibrosis.

Edema Severity:

Generally determined by comparing the circumference of the affected limb to the healthy limb at the same measurement point:

Mild edema: Circumference difference < 3 cm

Moderate edema: Circumference difference 3–5 cm

Severe edema: Circumference difference > 5 cm

Side of Affected Limb:

L, Left

R, Right

Measurement Instructions:

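### Ordered edema stage and severity fall under an unordered chi-square test, which costs power if TEAS shifts patients toward milder categories

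*Protocol article*

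**What the plan says.** The Data analysis section divides outcomes into two types.

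- **Categorical data.** "Enumeration data (categorical data) will be presented as percentages or constituent ratios", and "differences between groups will be analyzed using the Chi-square" test. No other between-group method is named for this type.
- **Measurement data.** A t-test if normal. Otherwise: "Measurement data that does not follow a normal distribution will be analyzed using non-parametric rank-sum tests".

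Tests are two-sided, and "A P-value < 0.05 will be considered statistically significant".

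Under Secondary outcomes, the item headed "Comparison of Limb Circumference Changes, Edema Staging, and Severity" makes stage and severity outcomes to be compared. Table 4 records both as tick-box categories. Its notes say "ISL Staging classifies lymphedema into 4 stages based on severity", numbered 0 to III. Severity is cut from the between-arm circumference difference into three grades, the middle one being "Moderate edema: Circumference difference 3–5 cm".

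The Sample size calculation section plans 30 per group, raised to 36 for dropout. It gives no power or effect size for stage or severity.

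**The concern.** A Pearson chi-square on a 2 × 4 table returns the same value if the stage columns are shuffled. It asks whether the two distributions differ in any way, and spends up to three degrees of freedom on that (two for severity). The question for a preventive treatment is narrower: do TEAS patients end up lower on the scale? A rank-based test puts one degree of freedom on that question.

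At stake is the chance of detecting a consistent shift toward milder stages in a trial of 72 patients. The primary incidence comparison is binary and has no ordering to lose, so this point does not touch it.

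**Working it through.** **1. Sample size.** The plan's figure reproduces: 30 × 2 × (1 + 0.20) = 72, or 36 per arm. After 20% loss, 36 × 0.80 = 28.8 remain, so about 30 evaluable per arm is a fair basis.

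**2. Degrees of freedom alone.** The noncentrality that gives 80% power on 1 df at two-sided 0.05 is (1.960 + 0.842)² ≈ 7.85. The same noncentrality gives 70.9% on 2 df and 64.5% on 3 df.

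**3. Assumed control mixes.** The protocol gives incidences only: about one quarter (Discussion), 58.3% after ALND and 77% by 3 years (both Introduction). Each was split over stages 0/I/II/III by assumption:
- 25%: 75/13/9/3
- 58.3%: 41.7/30/22/6.3
- 77%: 23/35/30/12

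Severity (mild/moderate/severe) was assumed as 80/15/5 or 60/30/10.

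**4. Assumed effect.** The cumulative odds are multiplied by a common odds ratio (OR). Example, 58.3% mix, OR 3: the odds of stage 0 are 0.417/0.583 = 0.715; times 3 is 2.146; 2.146/3.146 = 0.682. The full TEAS mix is 68.2/20.2/9.4/2.2.

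**5. Tests compared.** Pearson Σ(O − E)²/E against the tie-corrected Wilcoxon rank-sum test, two-sided 0.05, 30 per arm, 8,000 simulated trials per scenario. A second run of 20,000 trials per scenario agreed within 2 points. Losses are taken before rounding.

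| Outcome, control mix | OR | Chi-square | Rank-sum | Loss (points) |
|---|---|---|---|---|
| Stage, 25% | 2 | 9% | 18% | 9 |
| | 3 | 17% | 34% | 17 |
| | 4 | 24% | 46% | 21 |
| Stage, 58.3% | 2 | 17% | 29% | 12 |
| | 3 | 40% | 58% | 18 |
| | 4 | 57% | 76% | 19 |
| Stage, 77% | 2 | 20% | 30% | 10 |
| | 3 | 45% | 62% | 17 |
| | 4 | 65% | 82% | 17 |
| Severity, 80/15/5 | 2 | 10% | 16% | 6 |
| | 3 | 17% | 29% | 12 |
| | 4 | 24% | 38% | 14 |
| Severity, 60/30/10 | 2 | 17% | 24% | 6 |
| | 3 | 35% | 47% | 12 |
| | 4 | 52% | 64% | 12 |

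With all 36 per arm analysed, stage at OR 3 gives 21% vs 39% (25% mix), 48% vs 67% (58.3%) and 53% vs 71% (77%). The gap stays at about 18 to 19 points.

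**6. No treatment effect.** Chi-square rejects in about 3% (25% mix), 4.1% (58.3%) and 4.8% (77%) of trials. The tables are sparse: 85% to 100% of simulated stage tables had more than one fifth of cells with expected counts below 5. Here that makes the test slightly conservative, not liberal.

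**7. Effects that are not a common odds ratio** (stage, 30 per arm).

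| Pattern | Chi-square | Rank-sum |
|---|---|---|
| Incidence 58.3% to 29%, stage mix among cases unchanged | 46% | 60% |
| Incidence 25% to 8%, stage mix among cases unchanged | 23% | 43% |
| II/III move to I only, stage 0 fixed at 41.7% | 71% | 23% |
| II/III move to I only, stage 0 fixed at 75% | 26% | 6% |
| I moves to 0 only, II and III unchanged | 54% | 25% |

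The first two rows keep the rank-sum advantage. The last three reverse it.

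**The case against.** The strongest reply has four parts.

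- **Inference.** Data analysis does not name stage or severity. Their assignment to chi-square is read from a general sentence in a condensed article, and an SAP may say otherwise. This stands as a limit. Even so, the sentence covers categorical data without exception, and the rank-sum sentence is confined to measurement data. An SAP with an ordinal test would depart from the published text.
- **Assumed size.** No stage mix or effect is in the protocol. At OR 2 both tests are weak (9% to 20% against 18% to 30% for stage). This stands; hence the range.
- **Reversal.** The last three rows of the second table show chi-square ahead, one of them a pattern in which only stage I cases are prevented. This also stands. The case for a rank-based test is that a shift toward milder stages is the natural target of prevention, not that it wins against every alternative.
- **Importance.** These are secondary outcomes in a trial whose sample size rests on its exploratory nature. That limits the weight of the point but does not make the test fit the scale.

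A reader might infer more than the document supports:

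- *Stage and severity are the only graded measures of lymphedema.* They are not. Circumference at five points, the swelling VAS, the 11-item symptom score and ultrasound skin thickness are also graded, and severity is itself a cut of a circumference difference.
- *Sparse cells make the test invalid.* In these scenarios it does not inflate false positives.
- *Adverse-event tests are affected.* The Safety evaluation section plans only to summarise adverse events and specifies no between-group test.
- *The absence of an exact test for small counts is a defect.* That fallback is routine detail commonly left to an SAP.

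**Conclusion.** The point holds as a matter of efficiency for two secondary outcomes. As written, the plan tests ordered stage and severity as unordered categories. At about 30 per arm, with a one-directional shift of common odds ratio 2 to 4, this costs about 9 to 21 percentage points of power for stage and 6 to 14 for severity. Those sizes rest on assumed category mixes, anchored for stage to the protocol's incidence figures, and on the effect being a consistent shift along the scale. The direction of the advantage depends on that last assumption. The type I error rate is not a concern here. The change is worth making but does not bear on the validity of the primary comparison.

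**What to change.** In Data analysis, under categorical variables, add one sentence: edema stage and edema severity will be compared between groups with the Wilcoxon rank-sum test, or with a proportional-odds model reporting a common odds ratio and 95% CI. Choose one of the two in advance. Keep chi-square for nominal and binary data.

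**Cost.** No new data or visits, and the named software already offers both methods. With 10 participants enrolled as of July 2025, the sentence can be fixed before outcome data are examined. The price is less power for effects that are not a consistent shift, as the reversal rows show. The common odds ratio also assumes a roughly similar shift at each cut of the scale; the rank-sum test does not need this to be valid.
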